## Abstract

**Background:**

Chest pain is a common presenting complaint in the emergency department (ED). Despite the frequency with which clinicians evaluate patients with chest pain, accurately determining the risk of acute coronary syndrome (ACS) and sharing risk information with patients is challenging. The aims of this study are (1) to develop a decision aid (*CHEST PAIN CHOICE*) that communicates the short-term risk of ACS and (2) to evaluate the impact of the decision aid on patient participation in decision-making and resource use.

**Methods/Design:**

This is a protocol for a parallel, 2-arm randomized trial to compare an intervention group receiving *CHEST PAIN CHOICE *to a control group receiving usual ED care. Adults presenting to the Saint Mary's Hospital ED in Rochester, MN USA with a primary complaint of chest pain who are being considered for admission for prolonged ED observation in a specialized unit and urgent cardiac stress testing will be eligible for enrollment. We will measure the effect of *CHEST PAIN CHOICE *on six outcomes: (1) patient knowledge regarding their short-term risk for ACS and the risks of radiation exposure; (2) quality of the decision making process; (3) patient and clinician acceptability and satisfaction with the decision aid; (4) the proportion of patients who decided to undergo observation unit admission and urgent cardiac stress testing; (5) economic costs and healthcare utilization; and (6) the rate of delayed or missed ACS. To capture these outcomes, we will administer patient and clinician surveys after each visit, obtain video recordings of the clinical encounters, and conduct 30-day phone follow-up.

**Discussion:**

This pilot randomized trial will develop and evaluate a decision aid for use in ED chest pain patients at low risk for ACS and provide a preliminary estimate of its effect on patient participation in decision-making and resource use.

**Trial registration:**

Clinical Trials.gov Identifier: NCT01077037

## Background

Over 6 million adults present with chest pain in US emergency departments (EDs) each year, making chest pain the second most common presenting complaint [1]. Despite the frequency with which clinicians evaluate patients with chest pain, reliably detecting patients with acute coronary syndrome (ACS) remains a diagnostic dilemma. Data from U.S. EDs suggest that 2.1% of patients with acute myocardial infarction and 2.3% with unstable angina are missed [2]. A missed diagnosis of ACS may have substantial medical and legal implications [3]. As a result, clinicians initiate formal diagnostic testing for ACS at a very low risk threshold [4]. High sensitivity is ensured at the expense of specificity, resulting in large numbers of very low risk patients being admitted to ED observation units for urgent cardiac stress testing, increased likelihood of false positive stress testing, excessive exposure to ionizing radiation [5], and significant cost to the healthcare system.

Risk communication in a busy ED setting is also a challenge. When a patient presents to the ED with chest pain and the initial evaluation for non-cardiac etiologies is unrevealing, the focus of the evaluation shifts to estimating a patient's risk for ACS. Without the assistance of decision support tools, clinicians are challenged to precisely quantify risk and often resort to terms such as "low," "rare," or "uncommon" when communicating risk to patients. One recent study reported that patients often overestimate the level of potential harm when verbal descriptors are used to communicate risk [6]. To increase patient understanding of risk and optimize knowledge transfer between physicians and patients, we will develop and evaluate a decision aid that includes a precise estimate of the short-term risk for ACS described using prose phrases, numbers, and a pictograph to account for patients' preferred mode of understanding numerical information.

To date, the authors are unaware of any published research investigating the specific role and impact of shared decision making in patients at low risk for ACS. We hypothesize that patients infrequently participate in the decision to undergo prolonged observation and urgent cardiac stress testing and that the use of a decision aid to communicate both the short-term risk of ACS and the risks of ionizing radiation exposure will increase patient involvement in the decision making process, lead to a preference-based decision, and safely decrease resource use. To test our hypothesis, we will accomplish the following specific aims: (1) develop and refine *CHEST PAIN CHOICE*, a decision aid to communicate the short-term risk for an ACS and the available management options and (2) test the effect of *CHEST PAIN CHOICE*, in a randomized clinical trial, on patient knowledge, the quality of the decision making process, patient safety, and resource use.

## Methods

### Design

To evaluate the decision aid, we will conduct a patient-level single center pilot randomized trial. The Mayo Clinic Institutional Review Board has approved all study procedures.

### Setting

Patients and emergency physicians will be recruited from the Saint Marys Hospital ED at the Mayo Clinic, a tertiary care academic ED with an annual census of 73,000 patient visits. The trial will be conducted in the flow of routine patient care. This approach will enable us to test how the decision aid performs in the real-world setting.

### Participants

#### Inclusion criteria

Eligible providers will include clinicians (attending physicians, supervised residents, nurse practitioners and physician assistants) caring for patients with chest pain. Eligible patients will include adults (>17 years of age) presenting to the ED with a primary complaint of non-traumatic chest pain who are being considered for admission to the ED observation unit for urgent cardiac stress testing.

#### Exclusion criteria

The trial will exclude patients with an initial cardiac troponin T value above the 99^th ^percentile reference limit (Roche Diagnostics [Basel, Switzerland]; 99th percentile <0.01 ng/mL; lower limit of detection 0.01 ng/mL; 10% coefficient of variation 0.035 ng/mL) [7], known coronary artery disease (at least one 50% stenosis on cardiac catheterization, electrocardiographic changes [old or not known to be old] indicative of ischemia such as ST-T changes or left bundle branch block, perfusion defects or wall motion abnormalities on exercise, pharmacologic or rest imaging studies, or previous documentation of acute myocardial infarction) [8], cocaine use within 72 hours by the clinician's initial history, and pregnancy. Patients who cannot read English or have, in their clinician's best judgment, major communication barriers such as visual or hearing impairment or dementia that would compromise their ability to give written informed consent (or use the decision aid) will be excluded.

#### Participant recruitment

We have previously developed and validated an electronic notification system that is highly sensitive and specific for identifying potentially eligible participants presenting to the ED with chest pain as a primary complaint (sensitivity 97.8%, 95% CI 96.1-98.8; specificity 98.3%, 95% CI 98.0-98.5; positive predictive value 68.8%, 95% CI 65.4-72.9; negative predictive value 99.9%, 95% CI 99.8-100.0) [9]. Shortly after arrival to the ED, a study coordinator will receive electronic notification of potentially eligible participants in real time by both pager and email. In collaboration with the treating physician, the coordinator will confirm eligibility for the trial. The coordinator will then inform patients about the trial and obtain written informed consent. Patients will be consecutively enrolled 6-7 days per week when a study coordinator is available for enrollment.

### Interventions

#### Decision aid

The *CHEST PAIN CHOICE *decision aid prototype has been developed through an iterative process involving collaboration between designers and researchers, field-testing by patients and clinicians, and revision of the decision aid in response to the feedback provided. We have employed this methodology to develop the prior decision aids *STATIN CHOICE *[10] (assists providers in discussing the benefits and side effects of statins among patients with diabetes) and *OSTEOPOROSIS CHOICE *[11] (assists with the decision to take bisphosphonates among postmenopausal women at risk for osteoporotic fracture) [12,13].

#### Selection of a risk calculator for the decision aid

We recently conducted a systematic review to identify clinical prediction tools of sufficient diagnostic accuracy and methodological quality to consider for incorporation in clinical practice [14]. Of the clinical prediction tools that have been developed for ED patients with potential ACS, only 3 have been prospectively validated and thus could be considered for use in clinical practice - the Global Registry of Acute Coronary Events (GRACE) score, the Thrombolysis in Myocardial Infarction (TIMI) risk score, and the computerized quantitative pretest probability calculator. The GRACE risk score has been validated in only one ED study, and in this study data were not available to calculate a complete risk score in 26% of patients [15]. Although the TIMI risk score has been validated in over 17,000 ED patients in 5 different countries and can provide a reliable estimate of the risk for a cardiac event within 30 days of the ED visit, it has not undergone impact analysis [16]. The pretest probability calculator developed by Kline et al., unlike the TIMI risk score, has undergone impact analysis, demonstrating its true impact on patient care [17]. The pretest probability calculator was derived from data from 14,796 patients enrolled in the multicenter internet tracking registry of ACS database and prospectively validated in 8,120 ED patients with potential ACS [18]. The pretest probability calculator has since been prospectively validated in a multicenter study of 1,114 patients from 3 different academic EDs [19] and undergone impact analysis in a practical randomized trial [17]. For these reasons, we chose to use this calculator (Figure 1) to inform our decision aid *CHEST PAIN CHOICE*.

**Figure 1 F1:**
[figure not shown]
**Chest Pain Choice Decision Aid**.

#### Intervention arm

For patients randomized to the intervention arm, the study coordinator will review the contents of the decision aid in real time with the clinician immediately before the patient encounter. This approach to delivering the decision aid (with just-in-time training by the study coordinator prior to use) has been effectively used in our prior decision aid studies [22]. We have observed a trend towards superior results when the decision aid is delivered by the clinician compared to researchers delivering the tool prior to the clinical encounter [23].

#### Usual care

For patients randomized to the usual care arm, the clinicians will discuss the results of the diagnostic investigations and management options with the patient in that clinician's usual fashion. We will videotape the patient-clinician discussion for future review. No research-related interventions will be administered.

#### Outcome measures

Decision-based outcome measures take into account both the Ottawa Framework for Shared Decision Making [24] and self determination theory [25]. To assess the efficacy of the decision aid, we will measure the effect of *CHEST PAIN CHOICE *on the following outcomes: (1) patient knowledge regarding their short-term risk for ACS and the risks of radiation exposure; (2) quality of the decision making process for the patient and clinician; and (3) patient and clinician acceptability and satisfaction with the decision aid. We will also assess (4) the proportion of patients who decide to undergo observation unit admission and urgent cardiac stress testing; (5) economic costs and healthcare utilization; and (6) the rate of delayed or missed ACS (primary safety endpoint). The diagnosis of ACS will be considered delayed or missed if the patient was dismissed from the ED without observation unit admission and urgent stress testing and they meet the definition of ACS within 30 days of the ED visit. ACS will be defined as acute myocardial infarction [26], ventricular arrhythmia, cardiogenic shock, bradycardia requiring therapeutic intervention, or death attributed to a cardiac or unknown cause. Two investigators, blinded to allocation, will assess outcomes in all enrolled patients. A third investigator will resolve discordances.

A study coordinator will review the electronic medical record and conduct telephone follow-up for all enrolled patients starting at 30 days. The coordinator will verify the patient's telephone number at the time of enrollment to maximize the fidelity of follow-up. For those who are unable to be contacted by phone, we will use the resources of the Rochester Epidemiology Project [27] to determine outcomes for all Olmsted County residents and the social security death index [28] for patients who live outside of Olmsted County. We will note the success with enrollment and document the rate of 30-day follow-up.

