The discussion between the patient and clinician regarding the risks and benefits of further evaluation (i.e. observation unit admission with stress testing versus urgent follow-up with cardiology or follow-up with the patient's primary physician) and explanation of the *CHEST PAIN CHOICE *decision aid by the treating clinician will be video recorded to determine the degree of patient participation in the decision making process. We will use the OPTION scale [33] to evaluate the quality of the decision making on the video recordings. The scale enables an observer to quantify the extent to which clinicians involve patients in the decision making process. We have used the OPTION scale with adequate reliability in previous studies [22,34]. Video recordings will also provide information regarding the duration of the encounter (using video time stamps), fidelity of use of the tool, and difficulties encountered while using the decision aid.

We will conduct an economic evaluation of the trial using the Olmsted County Healthcare Expenditure and Utilization Database (OCHEUD). We will limit the analysis to subjects residing in Olmsted County, Minnesota since we have complete data on medical care utilization for this population. OCHEUD is a claims-based database that contains information on medical resource utilization, associated charges, and estimated economic costs for patients receiving care at either the Olmsted Medical Center or the Mayo Clinic and their associated inpatient facilities. Although the services provided represent the clinical practice patterns of Mayo Clinic and Olmsted Medical Center providers, the value of each unit of service has been adjusted to national norms by use of widely accepted valuation techniques. OCHEUD provides an estimated economic cost for each line item in the billing record and allows the aggregation of costs into categories deemed relevant to a particular study. The database serves as a major source of financial information on all patients (i.e., irrespective of payer) and includes line-item detail on date, type, frequency, and billed charge for every good or service provided. We will use data from the OCHEUD database to compare costs and utilization between the intervention and control groups. We will further compare the types of services that were used in each of the groups.

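### For unreached patients living outside Olmsted County, the fallback for the primary safety endpoint is a death index, which cannot show its four non-fatal components

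*Protocol article*

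**What the plan says.** All of this is in the protocol article, mostly under Outcome measures.

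- The sixth outcome, delayed or missed ACS, is labelled the primary safety endpoint. A case qualifies "if the patient was dismissed from the ED without observation unit admission and urgent stress testing and they meet the definition of ACS within 30", where the 30 counts days after presentation.
- "ACS will be defined as acute myocardial infarction [26], ventricular arrhythmia, cardiogenic shock, bradycardia requiring therapeutic intervention, or death" from a cardiac or unknown cause.
- Routine follow-up is the same for everyone: "A study coordinator will review the electronic medical record and conduct telephone follow-up for all enrolled patients starting at 30 days".
- When the telephone call fails, the source depends on residence. For residents, "we will use the resources of the Rochester Epidemiology Project [27] to determine outcomes for all Olmsted County residents"; the other group gets "the social security death index [28] for patients who live outside of Olmsted County".
- Blinded investigators classify every enrolled patient, and the completeness of 30-day follow-up will be documented. The article does not say whether a negative death-index search counts as completed follow-up.
- Under Data collection, the economic evaluation is restricted by residence because of data completeness: "We will limit the analysis to subjects residing in Olmsted County, Minnesota since we have complete data on medical care utilization for this population".

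**The concern.** The fallback for non-residents does not match the endpoint it serves. A death index can supply only the fatal component. Infarction, ventricular arrhythmia, cardiogenic shock and treated bradycardia can all occur in a patient who is alive at 30 days, and such a patient leaves no trace in the index. Residents who miss the call have a second source said to determine their outcomes. Non-residents who miss it have only the record review, which sees what was recorded in the system reviewed.

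The trial's hypothesis is that the decision aid reduces resource use safely. The patients who can have a safety event are those sent home without testing, and the aid is expected to increase their number. An undetected event in that group lowers the observed missed-ACS rate, more often in the arm whose safety is in question.

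**Working it through.** **Is there a safety figure to reproduce?** No. The article gives no expected event rate, margin or power for the safety endpoint, and neither the non-resident share nor the telephone non-contact rate. The only planning figures used here are the admission rates under Statistical considerations (90% control, 70% decision aid, 200 patients, stated power 95%).

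**Check of those figures.** Two-sided 5% test, 100 per arm, pooled variance under the null:

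- SE under the null = √(2 × 0.8 × 0.2 / 100) = 0.0566
- SE under the alternative = √(0.9 × 0.1/100 + 0.7 × 0.3/100) = 0.0548
- Power = Φ[(0.20 − 1.96 × 0.0566) / 0.0548] = Φ(1.63) = 94.8%, in line with the stated 95%.

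**Who can have a safety event.** Taking patients who are not admitted to the observation unit as dismissed:

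- Control: 100 × (1 − 0.90) = 10
- Decision aid: 100 × (1 − 0.70) = 30
- Total 40; ratio 30/10 = 3.

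**Which components each source can show, for a patient not reached by phone.**

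| Source | Applies to | Death | Four non-fatal components |
|---|---|---|---|
| Electronic record review | all patients | if recorded there | if recorded there |
| Rochester Epidemiology Project | county residents | yes, as stated | yes, as stated |
| Death index | non-residents | yes | no |

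**How many patients.** Affected = dismissed × share non-resident × share not reached. Both shares are assumptions.

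| Non-resident, unreached (assumed) | Control (10) | Decision aid (30) | Both (40) |
|---|---|---|---|
| 25%, 5% | 0.125 | 0.375 | 0.5 |
| 50%, 10% | 0.5 | 1.5 | 2 |
| 75%, 20% | 1.5 | 4.5 | 6 |

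If the record review found none of these patients' non-fatal events, and their risk equalled that of the other dismissed patients, the share of non-fatal events missed would run from 0.25 × 0.05 = 1.25% to 0.75 × 0.20 = 15%. Because the record review will find some, these are upper bounds under each assumption.

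**What one undetected event does.** Exact (Clopper-Pearson) upper limits of the two-sided 95% interval, decision-aid arm:

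- Among 30 dismissed: 0/30 gives 1 − 0.025^(1/30) = 11.6%. For 1/30, solving (1 − p)^30 + 30p(1 − p)^29 = 0.025 gives 17.2%.
- Among 100 randomised: 0/100 gives 3.6%; 1/100 gives 5.4%.

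**The case against.** Four points can be made against this.

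*The record review covers everyone.* A reader might infer that unreached non-residents are followed only through the death index. The same section contradicts that: the electronic record is reviewed for all enrolled patients, so an event treated within that system would be seen. This narrows the gap to non-fatal events treated elsewhere but does not close it. The restriction of the cost analysis to residents concerns a claims database, so it is only indirect evidence that non-residents' records are less complete.

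*No rule counts these patients as event-free.* A reader might infer that a negative death-index search is scored as no event. The wording can be read that way, since the index is listed among the sources used when the call fails and no unknown category is named. But no such rule is stated, and documenting the follow-up rate is compatible with treating these patients as incomplete. Classification may sit in an analysis plan that is not shown. What stands is the choice of source, which the article does state.

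*The numbers are small.* Applying the gap to all 200 patients would overstate it, because admitted patients cannot meet the definition. The affected group is a handful at most, and its size rests on assumed shares.

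*It is a pilot.* No safety threshold depends on this rate. That limits the stakes but does not remove them, since this is the designated primary safety endpoint and the results are meant to inform a larger trial.

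**Conclusion.** The point holds in a limited form. As written, the protocol under-ascertains the non-fatal part of its primary safety endpoint for non-residents who cannot be reached by phone, and does so differently by residence. It does not distinguish such patients from those with complete 30-day follow-up.

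At the planned admission rates, with the assumed shares, about 0.5 to 6 of 40 dismissed patients are affected (2 of 40 at 50% and 10%). The threefold weight on the decision-aid arm is a count. It follows from 30 versus 10 dismissed patients if the planned effect occurs and if residence and contact rates are the same in both arms. Among dismissed patients the affected fraction would then be equal; it is the rate per randomised patient that is understated by more in the decision-aid arm. The documents do not establish that any event would be missed, or that unknown outcomes would be scored as no event.

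**What to change.** 1. Classify a patient whose only 30-day information is a death-index search and the record review, with no component of the endpoint found, as vital status known, non-fatal outcome unknown. Do not count that patient as complete 30-day follow-up, or as event-free for the composite.
2. Report the number of such patients by arm among those dismissed without observation and stress testing.
3. Add a worst-case sensitivity analysis by arm in which each of them is counted as an event, beside the main safety rate.
4. Take a second contact number at enrolment, if the enrolment form (not shown) does not already ask for one. This has to be in place before follow-up, because no analysis rule can recover outcomes that were not collected.

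Cost: a few sentences of definition, one extra enrolment item, and a safety rate that is slightly less favourable or less precise. Retrieving records from outside hospitals would go further but needs resources the pilot may not have, and is not proposed.

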#### Data collection

We will survey patients and clinicians after each visit and videotape the decision aid discussion between the clinician and patient in both the intervention and control groups to capture outcomes. The patient surveys (see Additional files 1 and 2 for complete list of survey questions) will include:

• Items about level of education and income level for descriptive purposes

• Questions regarding the patient's comfort level in understanding different types of numerical information (e.g., fractions, percentages, graphs)

• 7 items to assess patient knowledge, 2 of which address the risks of radiation exposure, 2 that address the available management options, 2 about the potential implications of cardiac stress test results (not informed by content on the decision aid), and one question about the patient's personalized risk for ACS within 45 days of the ED visit. These items were fashioned after similar questions, which have demonstrated construct validity and responsiveness to the intervention in previous decision aid trials [29,30].

• 5 items using a 7-point Likert-type scale to assess the patient's perceptions about the amount, clarity and helpfulness of the information, their desire to receive information about other diagnostic options in the same way this information was delivered, and whether they would recommend the way they received information from their clinician during this encounter to other patients. We have used the same items in our previous trials [11,30].

• 10 items from the Trust in Physician scale [31]

• 17 items from the Decisional Conflict Scale [32], which assesses the extent to which the decision was informed, consistent with values, free of pressure, and effective

• Additional questions that inquire about the decision made by the patient during the visit and patient satisfaction with the degree of participation in the decision making process.

The treating clinician will be asked to complete a survey after each study visit (see Additional file 3). The survey includes questions regarding which decision the patient made, the clinician's perception of who made the decision, the clinician's confidence in the patient's understanding of the information, and questions regarding the acceptability of the decision aid.

The discussion between the patient and clinician regarding the risks and benefits of further evaluation (i.e. observation unit admission with stress testing versus urgent follow-up with cardiology or follow-up with the patient's primary physician) and explanation of the *CHEST PAIN CHOICE *decision aid by the treating clinician will be video recorded to determine the degree of patient participation in the decision making process. We will use the OPTION scale [33] to evaluate the quality of the decision making on the video recordings. The scale enables an observer to quantify the extent to which clinicians involve patients in the decision making process. We have used the OPTION scale with adequate reliability in previous studies [22,34]. Video recordings will also provide information regarding the duration of the encounter (using video time stamps), fidelity of use of the tool, and difficulties encountered while using the decision aid.

We will conduct an economic evaluation of the trial using the Olmsted County Healthcare Expenditure and Utilization Database (OCHEUD). We will limit the analysis to subjects residing in Olmsted County, Minnesota since we have complete data on medical care utilization for this population. OCHEUD is a claims-based database that contains information on medical resource utilization, associated charges, and estimated economic costs for patients receiving care at either the Olmsted Medical Center or the Mayo Clinic and their associated inpatient facilities. Although the services provided represent the clinical practice patterns of Mayo Clinic and Olmsted Medical Center providers, the value of each unit of service has been adjusted to national norms by use of widely accepted valuation techniques. OCHEUD provides an estimated economic cost for each line item in the billing record and allows the aggregation of costs into categories deemed relevant to a particular study. The database serves as a major source of financial information on all patients (i.e., irrespective of payer) and includes line-item detail on date, type, frequency, and billed charge for every good or service provided. We will use data from the OCHEUD database to compare costs and utilization between the intervention and control groups. We will further compare the types of services that were used in each of the groups.

